**Figure 2 figure2:**
[figure not shown]
The MindWave mobile device.

**Figure 3 figure3:**
[figure not shown]
A screenshot of one of the Focus Pocus mini-games.

### Procedure

#### Training

Prior to the surgery (usually the day before), participants will participate in an in-hospital intensive education (45-60 minutes) training session when they are not yet experiencing post-operative pain. During the training, an expert research assistant will explain to each patient how, when, and for how long the MindWave and the Focus Pocus app should be used. After that, the patient will be encouraged to practice the use of the tool by him/herself under the supervision of the research assistant. Once the patients become autonomous with the device, the training session will end, and the MindWave and tablet to be used until their discharge from the hospital will be provided.

#### Intervention Group (Neurofeedback and Usual Care)

Patients included in the intervention arm will continue to receive the standard care consisting of intercostal analgesia and intravenous pain killers. In addition to it, they will be encouraged to use the MindWave device to manage their pain on-demand and every time they think they need it. During the hospitalization period, patients assigned to the intervention group will also be asked to evaluate their pain over the past 12 hours on a daily basis until their discharge from hospital.

#### Control Group

Subjects assigned to the control arm will receive only the standard care. In adjunct, they will also be asked to evaluate their pain over the past 12 hours, every day starting from the operation until their discharge from hospital.

#### Randomization and Blinding

An independent researcher with no direct contact with the participants will use a computer-generated randomization with a 1:1 ratio and permutated blocks to optimize balance in each treatment arm. Due to the nature of the study, participants, care providers, and researchers cannot be blinded for the allocated treatment. However, the data analysis will be blind, as all of the patients receive a unique study code, under which their data is stored in the database.

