### Recruitment Procedure

All patients who are planned to undergo a thoracotomy for lung resection at the European Institute of Oncology, thoracic surgery unit, are considered potential candidates for the present study. Once admitted in the hospital, they will be screened by a trained research assistant to verify their eligibility. Eligible patients will be asked to sign the informed consent, and then randomly assigned to the intervention or control groups. All participants will be instructed to continue to receive medical care from physicians as usual. Subjects included in the intervention arm will be trained on the use of the technology and relaxation technique prior to the operation by a research assistant. They will also receive a MindSet device and tablet with the app Focus Pocus installed on it, for the entire duration of hospitalization (5 days).

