#### Secondary Outcomes

Several secondary outcomes will be measured at various time points during the hospitalization (Textbox 1). Clinical, radiological, and quality of life will be also assessed at the 2 follow-ups (at 1 and 4 months). The clinical and radiological assessment is part of the post-operative routine. However, it will be included in the outcome measures of the present protocol because we expect that a reduction of pain immediately after the operation can result in a better clinical and radiological long-term outcome. Quality of life will be also assessed using the EORTC QLQ-C30 (version 3.0).

Secondary outcomes measured.The number of events in which the patient reports severe, uncontrolled, and causing distress pain that requires urgent and unplanned care visitsOpioid consumption, measured quantitatively as oral morphine equivalent daily doseAnxiety, measured by the State-Trait Anxiety Inventory (STAI) scaleThe pattern of patient engagement with the MindWave tool, assessed quantitatively by the number and length of time each subject uses it (as recorded by the software). Usability and satisfaction with the tool will be also investigated.A blood test and chest x-ray will be also performed at the end of the hospitalization period in order to determine if the intervention group shows a better x-ray outcome and fewer infections, due to more physiotherapy because of reduced pain

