### Statistical Analysis

#### Sample Size Estimation

A sample size of 80 subjects, 40 per arm, is sufficient to detect a difference of 1.5 between the two groups (control vs intervention) in pain intensity scores, assuming equal standard deviation of 2.5, using a two-tailed *t* test of difference between means, with 80% power, and a 2-sided alpha of .05. Patients in the experimental group who decide to never use the device during hospitalization will be excluded from the study.

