#### Statistical Analysis

Statistical analysis will be conducted with the SPSS Software, version 22, with an alpha of .05 set a priori for all analyses. Descriptive statistics will be used to summarize baseline demographic characteristics by study arm. Continuous variables will be compared between the two groups using a *t* test and categorical variables will be compared using a chi-square test. Pain intensity, our primary outcome, measured longitudinally, will be assessed by mixed model analysis of variance with treatment assignment as the between-group factor and time as the within-subject factor. Effect sizes will be calculated as mean group differences with standard deviations. A similar approach will be used to analyze continuous secondary outcomes while categorical outcomes will be analyzed by chi-square tests.

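### The analysis is called blind because patients have a study code, but a code hides who the patient is, not which arm the patient is in

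*Protocol article*

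**What the plan says.** The Randomization and Blinding section of the protocol article first concedes that "participants, care providers, and researchers cannot be blinded for the allocated treatment". It then makes one exception: "the data analysis will be blind, as all of the patients receive a unique study code", and the data are kept under that code. The same section assigns the randomisation to an independent researcher who does not deal with patients. It mentions no masked arm labels, no withheld allocation list and no restriction on what the analyst receives.

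Three other parts of the article bear on this:

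- **Device only in one arm.** Recruitment Procedure: "Subjects included in the intervention arm will be trained on the use of the technology and relaxation technique prior to the operation", and these patients are given the headset and tablet. Control Group: "Subjects assigned to the control arm will receive only the standard care".
- **Device data as an outcome.** Secondary Outcomes lists engagement with the tool, "assessed quantitatively by the number and length of time each subject uses it (as recorded by the software", together with usability and satisfaction.
- **An exclusion in one arm.** Sample Size Estimation: "Patients in the experimental group who decide to never use the device during hospitalization will be excluded from the study".

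The Statistical Analysis section specifies a "mixed model analysis of variance with treatment assignment as the between-group factor and time as the within-subject factor" for pain intensity.

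**The concern.** The protocol presents the study code as the reason why the analysis is blind. A code separates the data from the patient's name. It does not separate the data from the treatment received, so the conclusion does not follow from the reason.

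This matters because analyst masking is the only blinding claimed in an otherwise open trial with a self-administered pain score as primary outcome. The article also leaves some choices open at analysis. It does not say whether the arm effect or the arm-by-time interaction decides the primary question. Pain rating is daily in the two group descriptions but every 12 hours under Primary Outcome, so the set of time points is not settled. An analyst who knows the arms could settle such points, and decide on exclusions, knowing which arm each choice favours. Readers of the eventual report would also credit the trial with a safeguard that the described mechanism does not provide.

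**Working it through.** No arithmetic decides this point. The check is to set the claim beside the provisions that it has to survive.

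1. **What the code does.** Each patient has a unique code and the data are stored under it. This conceals identity. Whether it conceals arm depends on what else is stored or passed on with the code, and the article is silent on that.

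2. **Whether the model itself breaks the blind.** It does not. The primary model needs a grouping variable, but a label A or B is enough. Blind analysis is therefore feasible.

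3. **Whether device data would break it.** Only intervention patients are given the headset and tablet; controls have standard care alone. A record with any use time, number of sessions, usability rating or satisfaction rating must therefore belong to an intervention patient. If those fields are in the file that the analyst opens, arm is known for every patient with an entry, whatever the arm label says.

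4. **Whether the exclusion rule would break it.** The rule refers to the experimental group and to absence of device use. Whoever applies it must know both. If the analyst applies it, the analyst knows the arm.

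5. **Whether the rule leaves a trace even if someone else applies it.** Allocation is 1:1 in permuted blocks with 40 planned per arm, so randomised numbers should be close to equal. If k never-users are removed and not replaced, the arms become about 40 and 40 − k. As an assumed illustration, k = 3 gives 40 against 37, and the smaller group is the likelier intervention arm. Losses among controls could blur this, and the article does not give an expected k. The rule could therefore help to identify masked groups; it would not do so with certainty.

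Steps 3 to 5 show that the blinding depends on safeguards that the article does not describe, and step 1 shows that the safeguard it does describe is not one of them.

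**The case against.** The strongest reply is that this is one condensed sentence in a journal article. Who holds the allocation list, how arms are labelled and which fields reach the analyst are matters often left to a full protocol or analysis plan, and neither is shown. That is fair as far as missing detail goes. It does not rescue the sentence, because the article does not leave the mechanism open: it names one, and the one named does not mask treatment.

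The reply does limit what can be concluded. A reader might infer any of the following, and the documents do not support them:

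- **That blind analysis is impossible or certainly absent.** It is feasible with masked labels and a restricted file. The text shows only that the stated reason is insufficient.
- **That the primary-analysis file contains the device data.** The article says that patients' data are stored under the code and that use is logged by the software. It does not say that these fields reach the person analysing pain.
- **That the analyst applies the never-user rule.** The article says that such patients are excluded, not by whom. Unblinded study staff could do it before data transfer.
- **That analyst blinding is the trial's sole protection against bias.** Randomisation by an independent researcher is another.
- **That the harm can be expressed as an inflated type I error.** Choosing afterwards between the main effect and the interaction does raise that error, but an analyst masked as A/B could make the same choice: swapping the labels leaves those tests unchanged. Bias from a one-arm exclusion is likewise the same whether or not the analyst is masked. Neither measures lost blinding.

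**Conclusion.** The point holds in this form: the study code cannot by itself make the analysis blind. The device-use, usability and satisfaction outcomes and the one-arm exclusion would reveal allocation if they reached the analyst, and unequal exclusions could help to identify even masked groups. This is a stated property that the stated mechanism does not deliver, rather than a detail left for another document.

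No magnitude is claimed and none can be derived from the article. The weight is moderate. The larger exposure in this trial is that patients who know their allocation rate their own pain, and masking the analyst would not change that. The conclusion rests on reading the code as the reason offered for the blinding, which is how the sentence is built. It also assumes that no separate document supplies the missing safeguards; if one does, the article's sentence should say so.

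**What to change.** Either make the claim true or remove it.

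To make it true:

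1. The independent researcher who generates the randomisation (assumed here to keep the list) prepares the primary-analysis file with arms labelled A and B and without device-use, usability or satisfaction fields.
2. All randomised patients stay in the primary analysis, with no exclusion confined to one arm. This removes the need for anyone to apply an arm-specific rule and the trace it could leave in the group sizes.
3. The analysis set, the time window for the pain scores and the decisive model term are fixed in writing before the file is opened.
4. The primary analysis is run on A/B. Only then are the labels and the engagement data released, and the engagement outcomes analysed.

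Otherwise, delete the statement that the analysis will be blind and describe the trial as open at every stage.

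The first route costs one data-handling step by someone already in the protocol and a few sentences of text. It needs no extra staff, patients or measurements. The second costs one sentence.

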### Outcome Evaluation

#### Data Collection Materials

We will assess one primary outcome and several secondary outcomes. A number of validated instruments will be used to assess the outcomes at multiple time points during the hospitalization and follow-ups. The patients, both in the treatment and in the control arms, will be asked to complete them at specific time-points without the supervision of the research assistants. Hospital nurses will be asked if they completed all the outcome measures, as requested by the protocol, at the end of each day. Demographic and clinical information of each participant will be also collected.

#### Primary Outcome

The primary outcome measurement is pain intensity, measured as a continuous outcome. It will be assessed quantitatively with the Numeric Pain Rating Scale (NRS) [47]. The paper version of the questionnaire will be self-administered. Participants will be asked to complete it starting from 12 hours after the operation, and every 12 hours during the entire hospitalization period.

#### Secondary Outcomes

Several secondary outcomes will be measured at various time points during the hospitalization (Textbox 1). Clinical, radiological, and quality of life will be also assessed at the 2 follow-ups (at 1 and 4 months). The clinical and radiological assessment is part of the post-operative routine. However, it will be included in the outcome measures of the present protocol because we expect that a reduction of pain immediately after the operation can result in a better clinical and radiological long-term outcome. Quality of life will be also assessed using the EORTC QLQ-C30 (version 3.0).

Secondary outcomes measured.The number of events in which the patient reports severe, uncontrolled, and causing distress pain that requires urgent and unplanned care visitsOpioid consumption, measured quantitatively as oral morphine equivalent daily doseAnxiety, measured by the State-Trait Anxiety Inventory (STAI) scaleThe pattern of patient engagement with the MindWave tool, assessed quantitatively by the number and length of time each subject uses it (as recorded by the software). Usability and satisfaction with the tool will be also investigated.A blood test and chest x-ray will be also performed at the end of the hospitalization period in order to determine if the intervention group shows a better x-ray outcome and fewer infections, due to more physiotherapy because of reduced pain

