**Objective:**

The aim of this study is to evaluate the effect of a neurofeedback-based intervention on controlling acute post-surgery pain and improving long-term recovery in patients who undergo thoracotomy for lung resection for non-small cell lung cancer (NSCLC) at an academic oncologic hospital.

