### Secondary Aims

Secondary outcomes include evaluating the effects of neurofeedback on (1) hospital utilization for pain crises, (2) daily opioid consumption, (3) level of anxiety, (4) participants’ pattern of engagement with the MindWave tool, and (5) blood test and chest x-ray results. Long-term outcomes also include clinical, radiological, and quality of life evaluations at the 1 and 4 month follow-ups.

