##  Methods

### Trial Design

This study is based on a 2-parallel group randomized controlled trial design (intervention vs usual care), with multiple in-hospital assessments and 2 follow-ups (at 1 and 4 months) based on clinical, radiological, and quality of life assessments. Follow-ups will coincide with the follow-up visits. The research design is shown in Figure 1.

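### Quality of life is scheduled at 1 and 4 months with no stated pre-randomisation QLQ-C30 and no baseline covariate, which gives up precision on a secondary outcome

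*Protocol article*

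**What the plan says.** The Protocol article names the instrument under Secondary Outcomes: "Quality of life will be also assessed using the EORTC QLQ-C30 (version 3.0". Timing is given in several places, and they agree:

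- Secondary Outcomes: "Clinical, radiological, and quality of life will be also assessed at the 2 follow-ups (at 1 and 4 months".
- Secondary Aims: "quality of life evaluations at the 1 and 4 month follow-ups".
- Trial Design: "2 follow-ups (at 1 and 4 months) based on clinical, radiological, and quality of life assessments".
- The Methods paragraph of the Abstract likewise describes quality of life as part of the two follow-ups.

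The list of secondary outcomes in the textbox covers pain crises, opioid use, anxiety, engagement with the device, and the blood test and chest x-ray. The QLQ-C30 is not on it.

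On data at entry, Data Collection Materials says "Demographic and clinical information of each participant will be also collected" and Statistical Analysis says "Descriptive statistics will be used to summarize baseline demographic characteristics by study arm". Neither mentions a quality-of-life score.

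The primary analysis is a "mixed model analysis of variance with treatment assignment as the between-group factor and time as the within-subject factor". The same section applies a similar approach to continuous secondary outcomes. No baseline covariate is named.

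**The concern.** The Objective in the Abstract covers "controlling acute post-surgery pain and improving long-term recovery in patients who undergo thoracotomy", and the QLQ-C30 is the only patient-reported instrument named for the two follow-ups. A patient's score at 1 or 4 months probably depends in part on the score before surgery. Without a baseline measure, that variation between patients stays in the error term of the treatment comparison.

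The sample is small: 40 per arm at most, before any loss to follow-up and before the removal of experimental-arm patients who never use the device. At that size, wider confidence intervals make a quality-of-life result harder to interpret. What is at stake is the efficiency of one secondary outcome.

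**Working it through.** **The plan's own figure.** The article gives no sample size, power or precision for quality of life. Its only calculation is for pain: difference 1.5, SD 2.5, 80% power, two-sided 0.05, 40 per arm. Those inputs give 2 × (1.960 + 0.842)² × 2.5² / 1.5² = 43.6, so 44 per arm (45 by the t test). Forty per arm gives 75.5% power by the t test. That discrepancy is a separate matter; only the 40 per arm is used below.

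**Inputs.**
- n = 40 per arm (Sample Size Estimation), taken as a maximum.
- Two-sided alpha 0.05 (same section).
- r, the correlation between baseline and follow-up score: not in the documents. Assumed range 0.3 to 0.7.
- Target difference 0.5 SD: an assumption for illustration, since the article sets none.

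**Follow-up scores alone, one visit.** SE = √(2/40) = 0.224 SD. The difference detectable with 80% power (noncentral t) is 0.63 SD. For a 0.5 SD difference the noncentrality is 0.5/0.2236 = 2.24, and power is 60%.

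**With the baseline score as covariate.** The variance is multiplied by 1 − r², so SE = 0.2236 × √(1 − r²) and the noncentrality is 2.236/√(1 − r²). The equivalent number per arm without a baseline is 40/(1 − r²).

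| r | 1 − r² | Variance cut | SE (SD) | Detectable difference (SD) | Power for 0.5 SD | Equivalent n per arm |
|---|---|---|---|---|---|---|
| none | 1.00 | – | 0.224 | 0.63 | 60% | 40 |
| 0.3 | 0.91 | 9% | 0.213 | 0.61 | 64% | 44 |
| 0.5 | 0.75 | 25% | 0.194 | 0.55 | 72% | 53 |
| 0.7 | 0.51 | 49% | 0.160 | 0.45 | 87% | 78 |

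Estimating the extra coefficient costs little: the detectable difference at r = 0.5 moves from 0.549 to 0.553 SD.

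**Average of the two follow-ups.** Assume one common correlation r among all three measurements. The variance, in units of the single-visit variance, is (1 + r)/2 without baseline and (1 + r)/2 − r² with it:
- r = 0.3: 0.65 to 0.56, a cut of 14%.
- r = 0.5: 0.75 to 0.50, a cut of 33%.
- r = 0.7: 0.85 to 0.36, a cut of 58%.

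**Plain change score.** Its variance factor is 2(1 − r): 1.4 at r = 0.3, 1.0 at 0.5 and 0.6 at 0.7. It is worse than using no baseline when r is below 0.5, and worse than the covariate model throughout this range.

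**Feasibility.** Recruitment Procedure gives the order: admission, screening by a research assistant, consent, then randomisation. Training for the intervention arm also takes place before the operation. There is therefore a research contact before allocation at which a questionnaire could be given.

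**The case against.** The strongest reply is that this is an argument from silence in a condensed article. The article does not say that quality of life is measured only at follow-up. Radiological assessment is also listed at the two follow-ups, yet a chest x-ray is planned at the end of hospitalisation as well, so a listing at follow-up is not exclusive. The design figure is not shown, Data Collection Materials speaks generally of several time points, and no time points are given for the anxiety scale either. This stands in part: an unlisted baseline cannot be ruled out. Still, every explicit statement of timing gives the follow-ups alone, and the model described has no place for a baseline score.

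A second reply is that nothing invalid has been shown. That stands. Randomisation allows a comparison of follow-up scores without a baseline, and the article sets no precision target for quality of life.

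A third is that the size of the gain rests on an assumed correlation. That also stands. At r = 0.3 the gain is modest.

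Three stronger readings are tempting, and the documents do not support them:

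- A reader might infer that long-term recovery has to be judged against the pre-operative state, so that the aim cannot be assessed without a baseline. The article defines no change-from-baseline quantity; its hypothesis compares the arms.
- A reader might count chance imbalance at baseline as a further harm. In a randomised comparison that imbalance is already reflected in the standard error, so it is the same loss of precision counted twice.
- A reader might suppose that patients already fill in study questionnaires before surgery. The article documents only screening, consent and, in one arm, training; pain ratings start 12 hours after the operation.

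The removal of never-users from one arm does weaken the randomised comparison. That is a separate problem, and a baseline score would not cure it.

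**Conclusion.** The point holds as a cheap improvement in precision for a secondary outcome. It does not show bias, an internal contradiction or an invalid analysis. With 40 per arm and an assumed correlation of 0.3 to 0.7, baseline adjustment lowers the variance at one visit by 9% to 49% and raises power for a 0.5 SD difference from about 60% to between 64% and 87%. At 0.5 the figures are 25% and 72%.

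These results depend on the assumed correlation, on all 40 per arm contributing data, and on the baseline entering the model as a covariate. With fewer patients the absolute power is lower, but the proportional cut in variance is the same.

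**What to change.** - Collect the QLQ-C30 after consent and before randomisation, at the admission contact described under Recruitment Procedure, and add this time point to Secondary Outcomes.
- In Statistical Analysis, state that the mixed model for the 1- and 4-month scores includes the baseline score as a covariate. Do not replace it with a plain change score.
- If a baseline QLQ-C30 is already collected, state it under Secondary Outcomes and add the covariate under Statistical Analysis.

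The cost is one extra short self-completed questionnaire per patient before surgery, with no new visit. A pre-operative score cannot be recovered once a patient has been operated on, so the change helps only patients not yet randomised.
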